#### General practices

Participating DOH general practices will receive written information on the study. GPs will be asked to give written informed consent to participate in the study and to share patient information from their electronic medical record system They will be encouraged to contact a member of the research team with their questions if anything is unclear.

#### Patients

##### Inclusion criteria

Patients will be eligible for the trial if all the following criteria are met: age > 18 years, being prescribed a cardiovascular or glucose-lowering drug for the first time by a DOH GP. The pharmacist will be signaled by his computer system when a patient visits with a first prescription.

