Furthermore, an implementation strategy is needed to provide tailored interventions in primary healthcare settings. For the efficient implementation of effective interventions in existing primary healthcare workflows, a good cooperation between pharmacists, GPs, practice nurses, and assistants is required. Technology-based systems that enable easy communication between healthcare providers about the progress of interventions and agreement about the allocation of time and resources need to be in place.

At Philips Research, a questionnaire was developed that creates a barrier profile based on an online assessment. The questionnaire consists of two parts: the Probabilistic Medication Adherence Scale (ProMAS), which is an 18-item questionnaire to assess nonadherence risk [12], and an additional 23 questions that assess the underlying barriers related to nonadherence. The resulting barrier profile provides insight into the extent to which eight cognitive, emotional, and practical barriers may hamper a patient’s adherence. For each of the identified barriers, a set of recommendations was formulated in a manual for healthcare providers on how to address the barriers in an intervention. Consequently, in patients starting chronic medication and at high risk for nonadherence, as assessed by ProMAS, the barrier profile provides an intervention strategy to overcome cognitive, emotional, and practical barriers to adherence at an early moment and thereby promotes adherence.

The primary objective of this study is to assess the effectiveness of using the medication-adherence tool in starters with cardiovascular medication, which includes antiplatelets, antihypertensives, and lipid-lowering drugs (Appendix), and oral blood glucose-lowering medication in the improvement of medication adherence as measured by pharmacy dispensing data. A second objective is to evaluate the implementation strategy to reduce barriers identified in patients at risk for nonadherence for a primary care setting relating to the acceptability of the workflow for all stakeholders (pharmacists, general practitioners, and patients).

The primary research question is as follows:What is the benefit of using the medication-adherence tool for medication adherence of patients starting with cardiovascular or oral blood glucose-lowering medication identified as being at high risk for nonadherence at a follow-up of 8 months compared to usual care?

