As in daily practice, patients receive a new medication from their community pharmacist; therefore, the assessment of patients’ medication adherence and potential barriers was most appropriately situated in the community pharmacy for our study. In the Netherlands, patients with a first dispensing of a chronic drug usually receive only an amount for 2 weeks. Treatment is continued after 2 weeks according to the experiences of the patient. Thus, patients starting with the study medication will have to have contact with the community pharmacy within approximately 2 weeks. This makes it convenient to ask eligible patients to participate in the study at the first dispensing, let them fill in the medication adherence assessment before the second dispensing, and apply the intervention when necessary at the second dispensing. The feasibility of implementing the use of the adherence tool in the daily pharmacy workflow was piloted in two pharmacies. During the pilot period, researchers regularly contacted the pilot pharmacists in order to track their experiences and any developments and to solve any issues. After the pilot period, a meeting between the research team and the two pilot pharmacists was planned for evaluation of the pilot. Based on the experiences during the pilot period, workflow adaptations leading to an increase in convenience and efficiency were made. Small changes in study information for patients, pharmacists, and GPs were made after the pilot period.

For further clarification of this study protocol, we reference the study flow diagram (Fig. 1) and the SPIRIT checklist (Additional file 1).

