### Recruitment of pharmacies, general practices, and patients

The trial will be carried out with pharmacists, general practitioners, and their patients with a first prescription of cardiovascular medication, including antihypertensives, antiplatelets, and lipid-lowering drugs, or oral blood glucose-lowering medication made by their GP within the study period (see Appendix for drug classes and ATC codes). A first prescription is defined as no drug dispensing from a drug class issued to the patient in the preceding year. For example, a patient who used a beta-blocking agent in the preceding year is not eligible when starting another beta blocker but will be eligible when starting a statin.

The primary care cooperation De Ondernemende Huisarts (DOH), or The Innovative General Practitioner, will play a key role in the recruitment of pharmacies and general practices for this study. DOH is a general practice collaborative, i.e., approximately 70 GPs working in 16 group practices in the southeastern part of the Netherlands who that share an overarching management structure and develop and implement structured care for several prevalent chronic conditions, including cardiovascular diseases and diabetes.

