##### Exclusion criteria

Patients will be excluded if they have any cognitive impairments or insufficient Dutch language skills as determined by the pharmacists' judgment. Inclusion numbers will be monitored; inclusion will be stopped when the targeted number is reached.

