#### Adherence

Medication adherence is calculated as the percentage of days covered by medication (PDC) based on pharmacy dispensing of one drug group since the start of the therapy until the end of the study period. Patients with a PDC of at least 80 % are labeled as “sufficiently adherent.” PDCs are calculated per medication group (see Appendix), except for blood glucose lowering drugs. As for diabetes, often, more than one drug is used, and patients have to adhere to each drug from the subclass, e.g. to biguanides and sulfanilamide derivatives. Data on dispensing will be based on routine pharmacy data collection.

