A measurement period of at least 8 months is preferred in order to get valid information from dispensing data. A first prescription is usually dispensed for 14 days, followed by a prescription for 90 days. After 8 months, at least two repeat prescriptions after the second dispensing must have had occurred to meet a PDC of 100 %. As we assume a PDC of 80 % is sufficient, at least (14 days + 180 days =) 196 days * 1.2 = 234 days = 7.8 months are needed to detect nonadherence. If the last patient was included after 14 months, together with the measurement period, this ends up the total study period with 22 months needed for follow up.

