## Appendix

### ATC codes for cardiovascular or oral blood glucose-lowering medication

- ATC code A10B: oral antihyperglycemic drugs
- ATC code B01AC: platelet aggregation inhibitors
- ATC code C01A: cardiac glycosides
- ATC code C01D: vasodilators
- ATC code C03: diuretic drugs
- ATC code C07: beta-blocking agents
- ATC code C08: calcium channel blockers
- ATC code C09: agents acting on the renin-angiotensin system
- ATC code C10: lipid-lowering drugs

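### Eligibility does not require intended continuing use, but the PDC outcome presumes it, so planned short-course starters can be enrolled and scored nonadherent while taking the drug as prescribed

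*Protocol article*

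**What the plan says.** All references are to the protocol article.

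- **Inclusion criteria.** Two conditions are listed, and meeting both makes the patient eligible: age over 18 and "being prescribed a cardiovascular or glucose-lowering drug for the first time by a DOH GP".
- **Recruitment of pharmacies, general practices, and patients.** First use is defined by looking back only: "A first prescription is defined as no drug dispensing from a drug class issued to the patient in the preceding year".
- **Exclusion criteria.** Only "any cognitive impairments or insufficient Dutch language skills" exclude a patient.
- **Appendix.** Nine whole ATC groups are listed without carving out any subgroup or indication, for example "ATC code C01D: vasodilators".
- **Adherence.** PDC is "based on pharmacy dispensing of one drug group since the start of the therapy until the end of the study period", and 80 % or more counts as sufficiently adherent. No rule covers an intended end of treatment or as-needed use.
- **Sample size.** The length of follow-up is justified by a supply pattern of long-term use: "A first prescription is usually dispensed for 14 days, followed by a prescription for 90 days".
- **Study design.** The workflow rationale is also about long-term drugs: "patients with a first dispensing of a chronic drug usually receive only an amount for 2 weeks".
- **Data analysis.** The primary analysis is by intention to treat, so an enrolled high-risk patient stays in.

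**The concern.** The rationale, the workflow and the outcome are built for chronic medication, but the criteria that the pharmacist applies do not say so. A patient whose first prescription in a listed group is a planned course of a few weeks meets every written criterion. That patient is then measured against a full follow-up of supply that was never intended.

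Three things would be at stake:

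- The primary comparison of high-risk patients would contain people whose PDC is below 80 % in either arm whatever the tool does, which pulls the difference towards zero.
- The reported nonadherence rate would be too high.
- The predictive values of the ProMAS and the barrier profile in the control group would be distorted, because some patients who follow their prescription would count as nonadherent.

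**Working it through.** **1. What a planned short course scores.** Eight months is taken as 240 days. The threshold is 0.80 × 240 = 192 days of supply. PDC = days supplied / 240.

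| Supply (days) | PDC | Label |
|---|---|---|
| 14 | 5.8 % | below 80 % |
| 30 | 12.5 % | below 80 % |
| 90 | 37.5 % | below 80 % |
| 104 (14 + 90) | 43.3 % | below 80 % |
| 194 (14 + 2 × 90) | 80.8 % | at least 80 % |

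A planned course under 192 days cannot be labelled adherent. If eight months is taken as 243.5 days, the limit is 0.80 × 243.5 = 194.8 days. For an as-needed prescription no daily quantity applies, so the number of days that a package covers is undefined and no PDC follows from the stated rule.

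**2. The plan's own sample size.** Inputs from the Sample size section: 60 % nonadherent in controls (40 % adherent), a gain of 20 points (60 % adherent), ICC 0.05, power 80 %, type 1 error 5 % (taken as two-sided), and 14 pharmacies (taken as 7 per arm).

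- Unclustered n per arm = (1.960 + 0.842)² × (0.4 × 0.6 + 0.6 × 0.4) / 0.2² = 94.2.
- Solving 7m / [1 + (m − 1) × 0.05] = 94.2 gives m = 39.06, which matches the stated 39 per pharmacy.
- 39 / 0.70 = 55.7, rounded up to 56, and 56 / 0.50 = 112. Both are as stated.

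**3. Effect of a share f scored below 80 % by design.** The document gives no value for f, so it is an assumption. If f is the same in both arms and the planned rates exclude such patients, the rates become 0.40(1 − f) and 0.60(1 − f). The effective number per arm at 39 per pharmacy is 7 × 39 / (1 + 38 × 0.05) = 273 / 2.9 = 94.1. Power = Φ( difference / √[(p₀(1 − p₀) + p₁(1 − p₁)) / 94.1] − 1.960 ).

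| f | Adherent, control vs intervention | Power at 39 per pharmacy | Evaluable per pharmacy for 80 % power |
|---|---|---|---|
| 0 | 40 % vs 60 % | 80.0 % | 39 |
| 5 % | 38 % vs 57 % | 75.8 % | 56 |
| 10 % | 36 % vs 54 % | 71.4 % | 92 |
| 15 % | 34 % vs 51 % | 66.8 % | 219 |

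From f = 20 % (32 % vs 48 %), 80 % power cannot be reached with 14 pharmacies at any number per pharmacy. At f = 5 %, the 56 evaluable patients needed equal the number that the plan enrols to allow for 30 % loss.

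**The case against.** **The document does not show that such patients exist in this trial.** It never says that any listed group is prescribed briefly or as needed. That is general knowledge about the drug classes, and no share is given. A reader might infer that such patients are enrolled in numbers, but the text supports only that they can be. This part of the objection stands.

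**Chronic use is implied in several places.** The Study design section speaks of a chronic drug. The ProMAS is adapted for patients who take no other chronic medication, which treats the study drug as chronic. The GP starts a treatment plan, the pharmacist judges eligibility, and an appointment for a second dispensing is made. These steps may filter out some very short courses. None is a criterion, and a course of, say, 90 days passes all of them.

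**An article condenses the full protocol.** That would answer a missing detail. Here the criteria are presented as complete and the PDC window is stated, and the two together give a wrong label.

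**The power loss may be overstated.** The 60 % nonadherence rests on published work that is not shown and may already include such patients. The plan counts on at least 14 pharmacies, and 25 are invited. Mean PDC is analysed too, and the calculation does not cover it. These limits stand.

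**Three stronger readings are not supported.**

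- As-needed starters are not certain to score below 80 %, because their days covered is undefined.
- The Appendix does not contradict the objective by listing cardiac glycosides and vasodilators. The Background describes cardiovascular medication as that "which includes antiplatelets, antihypertensives, and lipid-lowering drugs (Appendix", so the named types are examples and the Appendix is the operative list.
- Bias between arms is not shown. Pharmacists know their allocation and judge eligibility, so unequal shares are possible, but nothing indicates that they occur.

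**Conclusion.** The point holds as a mismatch between two stated rules. Eligibility accepts any first prescription in a listed group, while PDC presumes continuing supply to the end of follow-up. A planned course under about 192 of 240 days can enter the trial and is then labelled not sufficiently adherent even if taken exactly as prescribed. That follows from the document's own rules once such a patient is enrolled.

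The size is conditional. Power of about 76, 71 or 67 % instead of 80 % assumes a share of 5, 10 or 15 % that is equal in both arms, planned rates that exclude these patients, 14 pharmacies and the dichotomous outcome. The stated 39 per pharmacy is correct on its own inputs. The main effects are dilution of the primary contrast and distorted predictive values. The mismatch should be resolved before analysis, but the document does not show that it has harmed the trial.

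**What to change.** 1. Reconcile the inclusion criteria with the chronic-medication framing in the Background and Study design sections by stating that the index prescription must be intended for continuing use.
2. Define the PDC analysis set from the dosage instruction recorded at first dispensing, applying the same rule in both arms and blind to arm. Leave out index prescriptions that are as needed or a planned short course. The instruction predates the intervention, which starts at the second dispensing, so this selects on a baseline characteristic. It also avoids relying only on judgements by pharmacists who know their allocation.
3. Use the same set for the predictive values of the ProMAS and the barrier profile.
4. Report the full enrolled set as a sensitivity analysis, with a stated convention for days covered under as-needed prescriptions, and give the number left out in each arm.

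The cost is one sentence in the criteria and one filter on the dispensing data, with slightly fewer analysable patients. The filter relies on the recorded instruction. The document does not say whether that field is in the data extract, so this needs to be confirmed. An instruction that does not show the intended duration would leave some prescriptions unclassified, and a default for them should be fixed in advance.

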##### Exclusion criteria

Patients will be excluded if they have any cognitive impairments or insufficient Dutch language skills as determined by the pharmacists' judgment. Inclusion numbers will be monitored; inclusion will be stopped when the targeted number is reached.

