#### Pharmacies

The DOH cooperates closely with a number of community pharmacies (so-called CaZo cooperation). In total, 25 pharmacies have joined the cooperative. A representative of DOH will contact all 25 pharmacies connected to the DOH cooperation and provide them an invitation and an information leaflet about the study. Three members of the research team will visit all pharmacists who express their intention to participate. After a detailed explanation of the study aims, methods, and expected outcomes to the pharmacists, written informed consent for both participation and collection of de-identified patient data from the pharmacist’s database will be obtained.

The participating pharmacies are randomized for the intervention or control group, which implies that the patients are clustered within pharmacies. Pharmacies are stratified into small or large depending on their number of patients registered with DOH GPs. After the randomization procedure (drawing from a hat by an independent research assistant and consecutive allocation) has been performed, the pharmacies will be informed of their assignment to either the intervention group or the control group. Only pharmacists and pharmacy assistants from the intervention group are being trained to interpret the barriers to adherence profile and to provide tailored care. This prevents contamination between the intervention and control patients. Because patients in the Netherlands predominantly visit one pharmacy for all their medication, pharmacists are assumed to have complete medication dispensing information for their patients [13].

Due to the test of the medication-adherence tool, both pilot pharmacies will have to participate in the intervention group.

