### Outline of the study procedure for patients

For all patients starting with cardiovascular or oral blood glucose-lowering medication with a first prescription from a DOH GP, the GP starts a treatment plan in the electronic patient information system that the GPs and pharmacies use in their current daily practice. Then, the following process starts when the patient comes to the pharmacy for the first dispense.On first dispensing at the pharmacy, when the pharmacist considers the patient eligible for participation, the patient receives a short oral introduction to the study and an invitation to participate in the study.When the patient is interested in participation, the pharmacist asks for the patient’s permission to send the patient an email with a link to the study survey and collects the patient’s Citizen Service Number (CSN). Additionally, the pharmacist makes an appointment for the second dispense.The pharmacist (assistant) uses a tablet/web browser to register the patient for potential enrollment in the study.One week after the pharmacy visit, the computer system sends an email to the patient containing the link to the questionnaire.Then, the patient receives a paper-based package of study information and consent form to take home. This information will be provided on top of the usual information given during the first dispense in the pharmacy and will not replace any information that is usually provided during the first dispense.At home, the patient reads the study information and decides on participation. If the patient decides to participate, (s)he answers the link in the email received and completes the survey. The answers are used to produce a profile, which is sent to the electronic patient file system so that the pharmacists of the intervention practices have it available during the second dispensing appointment when the intervention starts (For control patients, the profile is only made available after completion of the study). The survey answers are retained until the end of the study.The patient sends the signed informed consent forms by regular mail in a pre-stamped envelope.For the second dispensing at the pharmacy, the pharmacists in the control arm do not receive the results of the medication adherence assessment from their patients, and they provide usual care. This includes the usual information at the start of a new drug as described in the guidelines of the pharmacists’ profession (KNMP richtlijn ‘ter hand stellen’, http://www.knmp.nl/praktijkvoering/bekostiging/begeleidingsgesprek-nieuw-geneesmiddel/knmp-richtlijn-ter-hand-stellen-juni-2013).The pharmacist in the intervention group checks whether the patient has completed the medication adherence assessment and takes care to provide a second dispensing of the drug.If the patient has not completed the assessment at the moment of the second dispensing, the patient is asked whether (s)he would like to participate and is asked to complete the survey in the pharmacy on a tablet.

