### Implementation of the medication-adherence tool

To deliver the tailored intervention, training on a patient-centered communication technique will be offered to the pharmacists, and one of the pharmacy assistants of the pharmacies assigned to the intervention group. Intervention pharmacists and their pharmacy assistants will receive a three-hour training session before starting the trial, consisting of a brief introduction to the proposed communication technique, demonstration of a second dispense moment with a barrier profile, and skills practice using role play. The pharmacists and pharmacy assistants will be specifically instructed on discussing the profile with the patients in order to offer a tailored intervention to overcome cognitive, emotional, or practical barriers.

Intervention pharmacies will also receive a manual containing instructions for discussing and overcoming the various potential barriers for medication adherence. In this manual, potential barriers are categorized into cognitive, emotional and practical nonadherence barriers. Furthermore, intervention pharmacies will receive a follow-up group session from the trainer on the patient-centered communication technique to provide support and exchange experiences on discussing the barrier profiles. In addition, three members of the research team will visit all participating pharmacists. At least the pharmacist and one experienced pharmacy assistant of a pharmacy will be present during that appointment. We will explain the study in detail and provide them with an easy-to-understand explanation of the workflow concept and subsequently discuss how the workflow concept can be optimally tailored to existing routine work procedures in the pharmacy. One of the researchers will be available during working hours to answer questions arising from the study. Finally, pharmacists will be offered the opportunity to contact one of the pilot pharmacists to ask questions and advices about the study procedures. Table 3 summarizes the various elements of the implementation strategy.

**Table 3 Tab3:** Elements of the implementation strategy

*■* Visit of the pharmacy by the research team to provide the manual and to tailor the workflow concept to existing work procedures in an optimal way
*■* Training session for pharmacists on patient-centered communication, using the manual and discussing the barrier profile
*■* Follow-up group session of the trainer on discussing the barrier profile

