## Discussion

This manuscript presents the protocol for a cluster-randomized clinical trial on the effectiveness of an adherence tool to improve medication adherence in starters with cardiovascular or oral blood glucose-lowering medication. A trial provides an optimal design to elucidate the effectiveness of interventions tailored to the underlying cognitive, emotional, and practical barriers to nonadherence identified for the patient. The results will provide insight in both the effectiveness of applying the medication-adherence tool and the predicting value of the ProMAS and the identified barriers for medication nonadherence. The effect of interventions to increase adherence depends on many factors. However, many approaches to improve adherence apply the one-size-fits-all-principle. By discussing the barrier profile with the patient, pharmacists can provide personalized support. An important and unique component of this study is the provision of an intervention tailored to the patient’s emotional, cognitive, and practical barriers. Not only the intervention itself, but also the implementation of the intervention will be tailored. The research team will visit all participating pharmacies to tailor the workflow concept as much as possible to existing work procedures. As the information on the barriers and the intervention is shared among the healthcare providers, all information supplied to the patient is consistent. A limitation of our study is that the questionnaire on barriers related to nonadherence has not been extensively used and validated in earlier studies. Furthermore, randomization occurs at the pharmacy level. Therefore, GPs may have patients in both the intervention and control group, which could lead to contamination. However, the barriers are discussed with the patients in the intervention pharmacies only. As the GPs will only follow a part of the intervention from the implementation guide for those patients that are announced by the intervention pharmacists, this limitation is presumably not severe. This study will be carried out in the DOH/CAZO care groups. These care groups have innovative mindsets. Consequently, the implementation of the intervention in other care groups might need additional guidance. Within these care groups, recruitment bias may be caused by the response of patients with certain characteristics, including medication adherence. Due to privacy legislation, the characteristics of nonresponders will not be analyzed.

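### Pharmacists who already know their arm decide by their own judgment whom to invite, so the arms may enrol different patients, and only baseline data on those enrolled could show it

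*Protocol article*

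**What the plan says.** All of this is in the Protocol article, under Methods/design unless stated otherwise.

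- **Allocation is known first.** Under Pharmacies, once the draw is done "the pharmacies will be informed of their assignment to either the intervention group or the control group". Under Implementation of the medication-adherence tool, "Intervention pharmacists and their pharmacy assistants will receive a three-hour training session before starting the trial".
- **The pharmacist then screens.** Under Inclusion criteria, "The pharmacist will be signaled by his computer system when a patient visits with a first prescription". Under Outline of the study procedure for patients, the next step depends on the pharmacist's view: "when the pharmacist considers the patient eligible for participation, the patient receives a short oral introduction to the study".
- **Exclusion is by judgment.** Under Exclusion criteria, "Patients will be excluded if they have any cognitive impairments or insufficient Dutch language skills as determined by the" pharmacist's own judgment. No instrument or threshold is named. The only monitoring mentioned there is of how many patients are included.
- **A second invitation is described after an intervention-arm step.** Under Outline of the study procedure for patients, "The pharmacist in the intervention group checks whether the patient has completed the medication adherence assessment". The next step is a repeat invitation with completion on a tablet in the pharmacy. No matching step is written for control pharmacies. A later paragraph does let online participants without home internet complete the survey in the pharmacy, without reference to arm.
- **Non-participants.** In the Discussion, recruitment bias through the kind of patient who responds is listed as a limitation, followed by: "Due to privacy legislation, the characteristics of nonresponders will not be analyzed".
- **Analysis.** Under Outcomes and Data analysis, the primary comparison is among enrolled patients at high risk on the baseline ProMAS. The multilevel model adjusts for age, gender, diagnosis and number of medications.

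**The concern.** Randomising pharmacies balances the pharmacies, and through them the people who use them. It does not balance the patients chosen afterwards by someone who knows the arm. Here the primary population is formed entirely after allocation, and the two exclusion grounds are elastic: any degree of cognitive impairment, and Dutch that is not sufficient for an unstated purpose.

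The workload also differs by arm. In an intervention pharmacy, a patient who scores high-risk commits the staff to a tailored conversation about barriers. In a control pharmacy the same patient receives usual care. Two pharmacists facing the same borderline patient may therefore decide differently. If the patients passed over would have been more or less adherent than the rest, the difference between arms contains a part that the tool did not cause. Neither cognition nor language is among the adjustment variables.

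**Working it through.** **1. Reproduce the plan's figures.** Inputs from Sample size: 60 % nonadherent, so 40 % adherent in the control arm; an effect of 20 %, read as 20 points (40 % to 60 %); ICC 0.05; power 80 %; type I error 5 %, taken as two-sided; 14 pharmacies, taken as 7 per arm.

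- Patients per arm without clustering: n = (1.96 + 0.84)² × (0.40×0.60 + 0.60×0.40) / 0.20² = 94.2.
- Patients per pharmacy: m = n(1 − ICC) / (k − n×ICC) = 94.2×0.95 / (7 − 94.2×0.05) = 39.06. The plan states 39.
- 39/0.70 = 55.7, so 56; and 56/0.50 = 112. Both are as stated.

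No stated figure is in dispute. These inputs only set the scale for what follows.

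**2. False difference if one arm passes over a fraction f of all high-risk starters whose adherence is q.** No true effect; f and q are assumptions, because the article gives no value for either.

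Apparent adherence = (0.40 − f×q) / (1 − f).

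| f | q = 30 % | q = 20 % | q = 10 % | q = 0 % |
|---|---|---|---|---|
| 5 % | +0.5 | +1.1 | +1.6 | +2.1 |
| 10 % | +1.1 | +2.2 | +3.3 | +4.4 |
| 20 % | +2.5 | +5.0 | +7.5 | +10.0 |

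Entries are percentage points above 40 %. For example, (0.40 − 0.10×0.30)/0.90 = 41.1 % and (0.40 − 0.20×0.30)/0.80 = 42.5 %. If the control arm is the one passing such patients over, the same shift appears with the opposite sign.

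**3. Upper bound when a fraction x of would-be nonadherent patients is passed over and no adherent one is.**

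Apparent adherence = 0.40 / (0.40 + 0.60(1 − x)).

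- x = 10 %: 42.6 %, a shift of 2.6 points.
- x = 20 %: 45.5 %, a shift of 5.5 points.
- x = 30 %: 48.8 %, a shift of 8.8 points.

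Here x is a share of the nonadherent 60 %, so it corresponds to 6 %, 12 % and 18 % of all high-risk starters. These are limits for those fractions, since they require the pharmacist to pick out future nonadherence without error.

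**4. What a shift does to the test.** Effective size per arm = 7×39 / (1 + 38×0.05) = 273/2.9 = 94.1. The standard error of the difference at 40 % in both arms is √(0.48/94.1) = 7.1 points. With a normal approximation and no covariates, the chance of a two-sided significant result with no true effect is about 6 % for a 2-point shift, 11 % for 5 points and 28 % for 10 points, against the nominal 5 %.

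**5. What the described data could show.** ProMAS and barriers are measured soon after the start in both arms, and the four model covariates will be held. Imbalance on these among enrolled patients is visible and can partly be adjusted for. Selection on anything else is not, nor is anything about starters who were never invited.

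**The case against.** Several points on the other side have force.

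- **A reader might infer that the trial could not detect selection at all.** The documents do not support that. Baseline ProMAS, barriers and covariates can be compared by arm. The article also says that pharmacies consent to collection of de-identified data from their databases, and that patients are registered for potential enrolment before they decide. So some denominators could be built. What remains out of sight is selection on factors not measured.
- **A reader might infer that nobody counts those passed over.** The article is silent on this. It is condensed, its flow diagram is not shown here, and a count may be kept. Nor does the privacy statement rule one out, since it concerns nonresponders' characteristics.
- **A reader might infer that the bias favours the intervention.** Direction cannot be read from the text. At first dispensing the ProMAS score is not yet known, and the plan assumes that only 40 % of starters will be high-risk, so the burden to be avoided is uncertain. Trained staff could equally favour patients who seem to need help. Nothing in the article links cognition or Dutch proficiency to dispensing-based adherence.
- **Recruitment after allocation is hard to avoid.** New starters do not exist when pharmacies are randomised. That explains the order of events, but not the open-ended exclusion rule.

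None of this removes the core: eligibility and invitation are judged by someone who knows the arm, under a rule without a threshold, and the limitation in the Discussion is not framed as a difference between arms.

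**Conclusion.** The point holds as a risk of arm-dependent selection that the stated rule leaves open, in either direction. It is not evidence that selection has occurred or that the trial is invalid.

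Its size depends on assumptions outside the documents. Where the patients passed over differ modestly from the rest (adherence 30 % instead of 40 %), passing over 10 % or 20 % of them shifts the comparison by 1.1 or 2.5 points. That is small beside the planned 20 and has little effect on the error rate. The 5.5 and 8.8 points are worst cases and should not be read as expected values. A shift near 5 points would roughly double the false-positive rate. The change is worth making because it is cheap and because the exclusion rates needed to narrow this range are not among the data that the article describes.

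**What to change.** In Exclusion criteria and Outline of the study procedure for patients:

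1. Invite every starter signalled by the computer system, in both arms, with the same script, and offer the same second-dispensing invitation on a tablet in both arms.
2. Allow exclusion only with a fixed reason code.
3. Use the existing registration page to log anonymous totals per pharmacy: signalled, excluded by code, not invited, declined, completed, and ProMAS of 13 or more.
4. Compare these totals, and baseline ProMAS, barriers and covariates, by arm during recruitment, and report them.
5. If exclusion rates differ by arm, add a sensitivity analysis. With an excess excluded fraction e and assumed adherence q, corrected adherence in that arm is (1 − e)×observed + e×q. Run it over a range of q, with q = 0 labelled as the worst case. Excluded patients have no ProMAS score, so the analysis must also state that their high-risk share is assumed equal to that of the others.
6. In the Discussion, name selection between arms as a limitation separate from patient response.

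The cost is a short entry for each signalled starter, about 6,081/25/12 = 20 per pharmacy per month, and one extra analysis. No nonresponder characteristics are needed, so the privacy constraint does not stand in the way. Two limits remain: applying a reason code still takes some pharmacist judgment, and recruitment was already under way at submission, so there may be no counts for patients passed over before the change. The steering committee confers weekly and may make adjustments, so the change can be made during recruitment.
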